#### Study Period

Depending on approval of the Local Ethics Committees, enrollment is planned to start from March 2019 and last until June 2020 or until the planned power calculation has been met.

#### Outcomes

The association between all the abovementioned variables and the following outcome variables will be assessed:

Primary outcome:

Adherence to planned chemotherapy in the first 12 weeks after the diagnosis in patients' groups stratified according to their baseline nutritional status.

Drug doses will be expressed in weight-based, body surface area (BSA)-based, AUC units or flat dose, according to standard dosing practice for a given drug or combination. For each drug in a regimen, the sum of the doses delivered during the first 12 weeks of therapy will be divided by the sum of the expected doses based on published standard schedule and dosing. The mean percent dose delivered of all drugs in a regimen will be reported as “percent of standard chemotherapy dose delivered.”

Similarly, the sum of the doses delivered during the first 12 weeks of therapy will be divided by the sum of the expected doses based on each patient's starting chemotherapy dose, and the mean percent dose delivered for all drugs in a regimen will be reported as “percent of planned chemotherapy delivered.” We will use percent of standard chemotherapy dose delivered to estimate the overall relative dose delivered, and we will use percent of planned chemotherapy dose delivered to quantify further dose reductions from starting dose and as an indicator of overall toxicity.

Secondary outcomes:

Percent of patients with chemotherapy-related toxicity in each group of patientsOS and survival at 6 monthsProgression-free survivalQuality of life that will be assessed using the European Organization for Research and Treatment of Cancer (EORTC) QLQ-PAN26 scaleNumber of hospitalizationsFactors associated with the percent of chemotherapy received.

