#### Variables

The following variables will be recorded in a dedicated Case Report Form (CRF).

All these measures are part of a standard workup of advanced PDAC patients and considered good clinical practice.

Patient-related:sex, race, age at diagnosissignificant comorbidities: chronic kidney failure, chronic heart failure, or respiratory insufficiency requiring oxygen treatmentMini-Nutritional Assessment (MNA) score. Primarily developed for elderly patients, MNA score was successfully used in the PreMiO study (Prevalence of malnutrition in patients at first medical oncology visit) to identify the risk of malnutrition or malnutrition among cancer patients at their first medical oncology visit (21):◾ 0–7 points: Malnourished◾ 8–11 points: At risk of malnutrition◾ 12–14 points: Normal nutritional statussarcopenia [measured with computed tomography (CT); fat-free mass is reduced; i.e., appendicular/L2 skeletal muscle mass index < 7.2 kg/m^2^ (men) or <5.5 kg/m^2^ (women)];cachexia [weight loss (WL) > 5% in the last 6 months, or WL > 2% if body mass index (BMI) < 20 kg/m^2^ or sarcopenia];12-item functional assessment of anorexia/cachexia therapy anorexia/cachexia subscale (FAACT-A/CS-12)a biliary stenta duodenal stenttotal and direct bilirubinECOG statusEuropean Organization for Research and Treatment of Cancer (EORTC) QLQ-PAN26 scale (22)Date of diagnosis, visit 1, visit 2 (3 months), and death/loss from follow-upCheck up on survival at 6 m

Tumor-related:Tumor site documented by endoscopic ultrasound, CT, or magnetic resonance imaging (head, body, or tail)Stage according to the TNM classificationVessels involvedPresence and site of metastatic diseaseAscitesCA-19-9Response evaluation criteria in solid tumors (RECIST) (23) (for visit 2)

Nutritional parameters:Leucocytes (lymphocytes, neutrophils), neutrophil-to-lymphocyte ratio, erythrocytes, hemoglobin, hematocrit, plateletsC-reactive protein, total protein, albumin, cholesterol, iron, transferrin, ferritin, magnesium, zincInternational normalized ratio, activated partial thromboplastin timeBlood fasting glucose, glycated hemoglobin

Pancreatic function and treatment:PEI will be defined by levels of fecal elastase-1 <200 mcg/g; pancreatic enzyme replacement therapy (PERT), date of starting PERT, the dosage of daily taken PERTDiabetes mellitus (DM), date of DM diagnosis, DM type, DM treatment

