Treatment-related:Planned chemotherapy protocolDosages of chemotherapy planned (mg/m^2^)Percent of standard chemotherapy dose deliveredPercent of planned chemotherapy deliveredChanges to the predefined schedule (dose reduction, schedule modifications, stop before planned)Date of treatment start and endAdverse events (National Cancer Institute toxicity scale for visit 2) (24).

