#### Description of the Intervention (Schedule of Visits)

Visit 1 (screening, within 1 month from initial diagnosis)

Patients will be informed about the study. Once patients agree with the inclusion in the study, we will evaluate the inclusion and exclusion criteria. Those patients who meet all the inclusion criteria and none of the exclusion criteria will be finally included in the study. In this visit, patient-related, tumor-related, and pancreatic function and treatment-related variables will be recorded, and quality of life questionnaire will be administered. The researcher will record weight, height, BMI, and unplanned WL % for the last 6 months.

Each patient's baseline nutrition status will be evaluated using the MNA score prior to starting chemotherapy. Patients will be classified as in the group with no nutritional risk, at risk of malnutrition, or malnourished.

Nutritional parameters and pancreatic function will be evaluated through blood tests and a fecal test.

Visit 2 (3 months after the first dose of planned chemotherapy)

The researcher will record in the CRF the planned chemotherapy, schedule, doses, dose reduction, and any adverse event^1^. The same variables recorded at Visit 1 will be checked again.

Check-up 3 (end of the study, 6 months)

The researcher will record in the CRF the OS and time until progression.

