Multivariable logistic regression analysis will be used to estimate the independent effect of malnutrition status on percent chemotherapy received (<80% chemotherapy received vs. 80% chemotherapy received; binary end point), after controlling for demographic and clinical characteristics (age, sex, race, ECOG status, tumor site, tumor stage, PEI, and DM). The demographic and clinical variables included in the final model will be chosen using a forward-stepwise method. Similarly, multivariable linear regression analysis will be used to estimate the independent effect of nutritional status on mean percent chemotherapy received (i.e., continuous endpoint), after controlling for demographic and clinical characteristics. All *p* values are two-sided with statistical significance evaluated at the 0.05 alpha level. Ninety-five percent confidence intervals (CIs) will be calculated to assess the precision of the obtained estimates (for odds ratios/beta estimates). The Kaplan–Meier method will be used to estimate OS and progression-free survival (PFS). The log-rank test will be used to compare OS and PFS between well-nourished patients and malnourished patients. Greenwood's formula will be used to calculate 95% CIs for Kaplan–Meier survival estimates. The frequency and percentage of missing values for each variable will be collected, analyzed, and reported (missing value analysis). All data will be anonymous once data collection is completed, respecting the confidentiality of the subjects participating, in accordance with data protection laws. All analyses will be performed in STATA 14 (Statacorp LLC, Texas).

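### The stated scope relates survival to variables known only at about 3 months, above all percent of dose delivered, with no landmark or time-dependent handling

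*Protocol article*

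**What the plan says.** The Outcomes section of the protocol article opens with the scope of the association analyses: "The association between all the abovementioned variables and the following outcome variables will be assessed". OS, survival at 6 months and PFS are among the outcomes that follow.

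The Variables section, to which that sentence points back, mixes baseline items with items that exist only after treatment has run for some time:

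- Tumour response: "evaluation criteria in solid tumors (RECIST) (23) (for visit 2".
- Toxicity: "events (National Cancer Institute toxicity scale for visit 2".
- Percent of standard and of planned dose delivered, schedule changes, and the treatment end date.

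For dose, the Outcomes section states that "the sum of the doses delivered during the first 12 weeks of therapy will be divided by the sum of the expected doses based on" either the published schedule or the patient's starting dose. It does not say that the expected doses stop accruing at death.

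The visit schedule fixes the timing: "Visit 2 (3 months after the first dose of planned chemotherapy" and "Check-up 3 (end of the study, 6 months".

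Statistical Analysis gives a method for one survival comparison: "The log-rank test will be used to compare OS and PFS between well-nourished patients and malnourished patients". Nutritional status for that comparison is scored before chemotherapy starts. The article states no landmark, no time-dependent covariate and no rule for patients who die before Visit 2.

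**The concern.** A variable that takes its value over the first 3 months cannot be treated as known at time zero. Patients who die in that period have less time to receive dose, to have an adverse event recorded or to be assessed for response. If they are kept in the low-dose, no-event or non-responder group, that group collects the early deaths by construction, and the other group gets a stretch of guaranteed survival.

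The background argues that patients helped to complete their planned treatment might benefit more from it. Readers will look to an association between dose delivered and survival to support that idea, and this is the association most exposed to the artefact. Toxicity could likewise look protective. For PFS there is also an overlap: progression recorded in the Visit 2 response category is itself a PFS event.

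**Working it through.** **The plan's own figures.** The article gives no number for any survival association. Its sample sizes supply the cohort size used below. They follow from the two-proportion formula with pooled variance under the null, two-sided 0.05 and 80% power:

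n = [1.960·√(2p̄(1−p̄)) + 0.842·√(p₁(1−p₁)+p₂(1−p₂))]² / (p₁−p₂)²

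For 70% versus 50%, p̄ = 0.60 and n = (1.3579 + 0.5708)² / 0.04 = 93. For 70% versus 55% and versus 60% it gives 163 and 356. All three match the article. The smallest design has 2 × 93 = 186 patients.

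**Why early death lowers the dose percentage.** Suppose doses are spread evenly and never exceed the expected amount.

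- A patient who dies at week 5 can receive at most 5/12 = 42%, however well treatment was tolerated.
- Reaching 80% requires survival to at least 0.80 × 12 = 9.6 weeks.
- The group at or above 80% therefore has no deaths in its first 9.6 weeks.

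**Share who die before Visit 2.** With exponential survival this is 1 − 0.5^(3/median in months): 29% for a median of 6 months, 21% for 9 and 16% for 12. The Background section gives about 6 months for gemcitabine alone. The 9 and 12 are assumptions for intensified regimens.

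**Simulation under no true effect.** Each setting used 1,000 cohorts of 186. Each later variable was generated independently of the survival hazard:

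- Dose: tolerated fraction from Beta(5, 1.25), mean 5/6.25 = 0.80. Delivered = tolerated fraction × min(T, 12 weeks)/12 weeks, cut at 80%. The cut is borrowed from the article's logistic model.
- Adverse event: time to event exponential, 50% by 3 months, counted only if it occurs before death.
- Response: 30%, counted only if alive at 3 months.

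The time-zero analysis keeps early deaths in the low-dose, no-event or non-responder group. The landmark analysis starts at 12 weeks for dose and at 3 months for the other two. Ranges run over the three medians. A false positive is a log-rank |z| above 1.96.

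| Variable | Follow-up | Time-zero hazard ratio | Time-zero false positives |
|---|---|---|---|
| Dose ≥80% vs <80% | 6 months | 0.35–0.36 | 95–100% |
| Response | 6 months | 0.37–0.40 | 70–95% |
| Any adverse event | 6 months | 0.60–0.63 | 40–66% |
| Dose ≥80% vs <80% | 24 months | 0.58–0.68 | 63–94% |
| Response | 24 months | 0.66–0.74 | 31–62% |
| Any adverse event | 24 months | 0.76–0.84 | 18–43% |

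With the landmark, the hazard ratio was 0.99–1.02 and false positives were 4–7% in every setting. Dropping patients who died before the measurement time, with the clock left at time zero, gave the same results.

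A separate dose simulation varied the assumptions: tolerated fraction with mean 0.75 or 0.85, median 6 to 11 months, 26 weeks of follow-up. The hazard ratio for <80% versus ≥80% was 2.6 to 3.6 from time zero, with 91–100% false positives. With a 12-week landmark it was about 0.95 to 1.0, with 4–5%. The inverse of 0.35 is about 2.9, so the two simulations agree.

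**The case against.** The strongest reply is that the article never specifies a time-zero analysis of these variables. Its one survival comparison with a named method uses nutritional status scored before chemotherapy, which needs no landmark. The opening sentence of Outcomes is generic and cannot be taken word for word: the recorded variables also include the date of death, and dose delivered is itself the primary outcome. Dose is otherwise given different uses, as a measure of treatment received, as a toxicity indicator and as a dependent variable in regression. The hypothesis and aims concern nutrition and exocrine function, not dose and survival. Time origins and landmarks are also commonly left to an analysis plan, and none is shown here.

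Most of this stands. A reader might infer that the planned OS and PFS comparison by nutritional status is biased, that a naive analysis has been prescribed, or that response and toxicity are bound to be distorted as badly as dose. The documents support none of these. A patient who dies before Visit 2 has no Visit 2 response assessment, and if such patients are excluded the artefact is gone.

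What remains does not rest on a missing detail. The article sets a scope that pairs later variables with survival. For dose delivered, the definition as written gives an early death a computable low value, so such a patient would not drop out as missing.

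**Conclusion.** The point holds for the stated scope of the secondary survival associations and goes no further. Followed from time zero for dose delivered, that scope can produce a hazard ratio of about 0.35 with no true effect at 6-month follow-up, and false positives in more than 90% of runs. For adverse events and response, the effect ranges from none to strong, according to how deaths before Visit 2 are classed. PFS has the added overlap with Visit 2 progression, which was not simulated.

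The sizes rest on assumptions that are not in the documents: exponential survival, medians of 9 and 12 months, the dose-tolerance distribution, the adverse-event and response rates, the 24-month follow-up, and treatment continuing until death or week 12. The direction for dose does not depend on these details. It follows from a fixed 12-week denominator.

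**What to change.** In the Outcomes section, limit associations with OS, 6-month survival and PFS to Visit 1 variables, using Visit 1 values of anything measured at both visits. Where dose delivered, adverse events or tumour response are to be related to survival, start the clock at a fixed landmark 3 months after first dose. Include only patients alive then, and also progression-free for PFS. Alternatively, enter these variables as time-dependent; for dose, this means delivered over expected up to each date. Twelve weeks is 12/4.345 = 2.76 months, so the dose window has closed by a 3-month landmark.

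This takes a sentence or two. The cost is precision in these secondary analyses, because early deaths drop out. With 186 patients, exponential survival and 6-month follow-up:

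- Median 6 months: usable deaths fall from 186 × 0.50 = 93 to 186 × (0.707 − 0.500) ≈ 39.
- Median 12 months: usable deaths fall from 186 × 0.293 ≈ 54 to 186 × (0.841 − 0.707) ≈ 25.

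The landmark results also apply only to patients who reach 3 months, and should be reported that way.

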Cachexia and malnutrition not only represent symptoms of the disease but also are important factors having a significant impact on the outcome of PDAC patients (9). A low value of fecal elastase-1, depicting impaired exocrine pancreatic function and contributing to cachexia, has been reported to strongly correlate with poor survival in advanced PDAC patients (10). However, cachexia and impaired nutritional status might also affect the tolerance and response to medical treatments such as chemotherapy. This is particularly important in PDAC; not more than 20% of patients are eligible for the resection at the time of the diagnosis (3), while the rest might have an indication for chemotherapy. In this setting, while Gemcitabine mono-chemotherapy has for a long time been the standard treatment for unresectable PDAC with relatively poor effect represented by a median overall survival (OS) around 6 months (11), intensified regimens, such as the combination of 5-fluorouracil, leucovorin, irinotecan, and oxaliplatin (FOLFIRINOX), or the addition of Nab-Paclitaxel to gemcitabine, are nowadays more frequently used, with substantially improved survival (12–17). However, due to their side effects, particularly encountered in FOLFIRINOX, intensified regimens can be less tolerable, leading to dose reduction or therapy discontinuation (13–15), which makes their use limited to the patients with ECOG status of 0, 1, and 2 (15, 16). For patients with ECOG of 3 or higher, the large majority of experts recommend best supportive care (18).

Considering this, it is even more important to assess the impact of the nutritional status in patients with advanced PDAC in order to identify sub-groups at a higher risk of side effects and treatment discontinuation. If timely identified, these patients could be approached and treated accordingly, in order to increase their capacity to complete the planned therapy and therefore possibly improve its efficacy. Studies so far conducted to address this important issue have been too few and limited in terms of parameters evaluated as well as outcomes observed and often did not use standardized measures. Hence, evidence is sparse and heterogeneous.

We, therefore, designed a multicenter prospective study in order to assess the impact of patient's nutritional status on the clinical course of advanced PDAC patients receiving chemotherapy.

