#### Statistical Analysis

The STROBE guidelines for observational studies will be followed to report our findings^2^. Descriptive statistics (including mean, standard deviation, median, range, frequency, and percent) will be calculated to characterize the study cohort.

Chemotherapy dosing over the first 12 weeks of therapy (i.e., percent chemotherapy received in the first 12 weeks, as defined above) will be compared between well-nourished and malnourished patients. Two-sample *t*-tests/Wilcoxon rank-sum tests will be used for MNA comparisons of mean/median percent chemotherapy received, for all patients and stratified by risk for toxicity. Two-sample *t* tests/Wilcoxon rank-sum tests and chi-square tests/Fisher's exact tests will be used, as appropriate, to compare malnutrition status between groups based on MNA, on demographic/clinical characteristics of interest.

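### Percent of planned chemotherapy delivered is an all-cause measure, so using it to indicate toxicity is biased against any group that dies or progresses sooner

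*Protocol article*

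**What the plan says.** The Outcomes section of the protocol article defines two ratios. The main one, percent of standard dose, compares delivery with the published schedule. The other, percent of planned dose, is built in the same way: "the sum of the doses delivered during the first 12 weeks of therapy will be divided by the sum of the expected doses", where the denominator is "the sum of the expected doses based on each patient's starting chemotherapy dose". The ratios are averaged over the drugs in the regimen. The section then assigns the second ratio a meaning: the study will use "percent of planned chemotherapy dose delivered to quantify further dose reductions from starting dose and as an indicator of overall toxicity".

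Four other places bear on this:

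- **Variables, treatment-related list.** The study records changes "to the predefined schedule (dose reduction, schedule modifications, stop before planned", together with treatment start and end dates and adverse events on the National Cancer Institute scale. The list names types of change and gives no reasons.
- **Outcomes, secondary list.** The percentage of patients with chemotherapy-related toxicity is a separate outcome, as are overall and progression-free survival.
- **Schedule of Visits, 6-month check-up.** "The researcher will record in the CRF the OS and time until progression".
- **Background.** Cachexia and malnutrition "are important factors having a significant impact on the outcome of PDAC patients". The Hypothesis section likewise expects an adverse effect on clinical course.

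**The concern.** A dose that was not given lowers the ratio whatever the cause. The definition neither ends the expected dose at death, progression or withdrawal nor limits the shortfall to changes made for toxicity. Full stops are foreseen, since early stopping is one of the recorded types of change.

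This would do little harm if the other causes were balanced between the groups. Here they are not expected to be: the exposure is malnutrition, and the protocol anticipates a worse course in malnourished patients. Death and progression would then remove more dose in that group, and the ratio read as toxicity would differ with no difference in toxicity. The error runs in the direction of the study hypothesis, so it is unlikely to be noticed as an anomaly. At stake is a statement that malnutrition makes chemotherapy more toxic when the data show only that malnourished patients stayed on treatment for less time.

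**Working it through.** **The plan's own figures.** The document gives no expected value for percent of planned dose. Its only related figures are the sample sizes of 93, 163 and 356 per group. They reproduce exactly as a comparison of two proportions (70% against 50%, 55% and 60%; two-sided 0.05; power 80%) and are not affected by this point.

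**Structure of the bias.** Let t be the fraction of the starting dose delivered while a patient is on treatment, equal in both groups because toxicity is assumed equal. Let f be the mean fraction of the 12 weeks that a group stays on treatment. If the expected dose covers the whole window:

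- mean ratio = t × f
- gap = t × (f in well-nourished − f in malnourished)

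The gap is zero only if f is equal in both groups. Its sign needs no further assumption; its size does.

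**Illustration 1: death alone, no toxicity (t = 1).** Assume exponential survival from the start of treatment. With median m months and 12 weeks = 2.76 months, set x = ln 2 × 2.76 / m. Then f = (1 − e^(−x)) / x.

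| Median survival | x | 1 − e^(−x) = dead by 12 weeks | f | Dose lost |
|---|---|---|---|---|
| 4 months (assumed) | 0.4783 | 0.3801 | 0.795 | about 21 points |
| 6 months | 0.3188 | 0.2730 | 0.856 | about 14 points |
| 9 months (assumed) | 0.2126 | 0.1915 | 0.901 | about 10 points |

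Only the 6-month value stands in the document: the Background reports a "median overall survival (OS) around 6 months" for gemcitabine alone. The resulting gaps, well-nourished against malnourished, are:

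- 9 v 6 months: 0.901 − 0.856 = 0.045, about 4.5 points
- 6 v 4 months: 0.856 − 0.795 = 0.061, about 6 points
- 9 v 4 months: 0.901 − 0.795 = 0.106, about 11 points

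**Illustration 2: stops for any cause other than toxicity.** Assume t = 85% in both groups, and that a share q of patients stops for death, progression or choice and loses half the 12-week dose on average. The mean ratio is 0.85 × (1 − q/2). None of these inputs is in the document.

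| q, well-nourished | q, malnourished | Mean ratios | Gap |
|---|---|---|---|
| 10% | 20% | 80.8% v 76.5% | about 4 points |
| 10% | 30% | 80.8% v 72.3% | 8.5 points |
| 15% | 40% | 78.6% v 68.0% | 10.6 points |
| 10% | 50% | 80.8% v 63.8% | 17 points |

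For scale, the smallest difference in the Power Size Calculation is 10 points, stated for chemotherapy delivered. If the planned-dose ratio were compared by a two-sample test with 163 per group and an assumed standard deviation of 25 to 30 points, the first two rows would be significant with probability of about 25–34% and 73–87%, although toxicity is identical.

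**The case against.** The strongest reply is that the phrase carries little weight in the plan, and much of that reply stands.

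- **It is one indicator, not a definition.** A reader might infer that the plan equates lost dose with toxicity. It does not: quantifying reductions from the starting dose is named first, and the toxicity use is as an indicator.
- **Toxicity is measured directly.** The percentage of patients with chemotherapy-related toxicity is a named secondary outcome, with graded adverse events. A reader might infer that the study will conclude that malnutrition raises toxicity when it does not. That would require the ratio to be preferred over the named outcome, and nothing in the document says so.
- **No test is tied to the toxicity reading.** The Statistical Analysis section says "Two-sample *t*-tests/Wilcoxon rank-sum tests will be used for MNA comparisons of mean/median percent chemotherapy received". The Abstract reports the main outcome as percent of standard dose.
- **The case report form may hold reasons.** The article only summarises it, so the absence of a reason from the list does not show that none is collected. Treatment-end, death and progression dates are collected in any case and would identify many stops at death or progression, though not those by patient choice.
- **The full 12-week denominator is an inference.** It is the natural reading, and no truncation is stated, but the text does not say how expected doses are counted after death.
- **The illustrative survivals may be pessimistic.** The Background says that intensified regimens with substantially better survival are now more often used, and patients with ECOG 3 or higher are excluded. A 4-month median implies about 38% dead by 12 weeks, which nothing in the document supports.

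These points reduce the weight and leave the size open. They do not remove the core point. The toxicity use of an all-cause ratio is stated in the document rather than left to an unseen one, and a reason field or a set of dates helps only if the indicator is defined to use it.

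**Conclusion.** The point holds as one about direction and interpretation. Under the natural reading, in which the expected dose is not cut off at death, progression or withdrawal, percent of planned dose mixes toxicity with every other cause of lost treatment. If malnourished patients die or progress sooner, it is biased toward showing more toxicity in them.

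The size cannot be derived from the document. The gap of about 6 points rests on exponential survival, medians of 6 and 4 months and no toxicity; other assumed inputs gave about 4 to 17 points. A reader might take any of these as an estimate of the bias in this study, but the document does not support that, since only the 6-month median is stated there and it belongs to gemcitabine alone.

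The main outcome and the sample size are untouched. The point deserves correction because the wording favours the hypothesis and is cheap to change, not because a principal conclusion depends on it.

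**What to change.** 1. In Outcomes, describe percent of planned chemotherapy as all-cause dose delivery relative to the starting dose, and delete the statement that it indicates overall toxicity.
2. Base conclusions about toxicity on the direct secondary outcome: the percentage of patients with chemotherapy-related toxicity, with National Cancer Institute grading.
3. If a dose-based toxicity indicator is still wanted, define it as shortfall attributed to toxicity, using the recorded reason for each reduction, delay or stop. Add that field if the case report form lacks it. At the least, use the treatment-end, death and progression dates already collected to separate shortfall due to death or progression.
4. Report that indicator beside the all-cause figure.

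The cost of the first two items is a change of wording. The third may need one field filled from the treatment record. Its drawback is investigator judgement: toxicity and patient choice overlap, and the article describes no blinding to nutritional status, so coding could lean toward the hypothesis. That is why the all-cause figure should stay in view. The date-based option avoids most of this judgement but cannot identify stops by patient choice.

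### Toxicity is graded only at Visit 2, so symptoms of malnutrition or exocrine insufficiency that predate the first dose may be misattributed to chemotherapy, more often in the malnourished group

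*Protocol article*

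**What the plan says.** The Outcomes section of the protocol article gives, as the first of the secondary outcomes, "Percent of patients with chemotherapy-related toxicity in each group". Under Statistical Analysis the main comparison is between well-nourished and malnourished patients as classified by the MNA.

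The treatment-related list under Variables includes adverse events and attaches the National Cancer Institute toxicity scale to visit 2. The Schedule of Visits agrees. At Visit 2, three months after the first dose, "The researcher will record in the CRF the planned chemotherapy, schedule, doses, dose reduction, and any adverse event".

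For Visit 1 the schedule says that "patient-related, tumor-related, and pancreatic function and treatment-related variables will be recorded, and quality of life questionnaire will be administered". Visit 1 also includes weight, BMI, recent unplanned weight loss, blood tests and a fecal test. It names no grading of symptoms on the toxicity scale. For Visit 2 the schedule adds: "The same variables recorded at Visit 1 will be checked again".

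The article also uses the share of planned dose delivered "to quantify further dose reductions from starting dose and as an indicator of overall toxicity".

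**The concern.** The exposure and the outcome overlap. Loss of appetite, weight loss, fatigue, anaemia, low albumin and diarrhoea can mark malnutrition or exocrine insufficiency before any drug is given, and the same terms can be recorded as adverse events afterwards. If they are commoner at baseline in the malnourished group, and the only grading takes place three months into treatment, some may be credited to chemotherapy. Any such error would fall unevenly, because the groups are formed on the characteristic that produces the symptoms.

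The Background gives the purpose of the study as finding subgroups at higher risk of side effects and of stopping treatment. A spurious excess of toxicity in malnourished patients would be taken as direct support for that hypothesis. The timing also matters for repair: a symptom grade not taken before the first dose cannot be reliably reconstructed by a later analysis plan.

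**Working it through.** **The plan's own figures.** The article gives no rate, effect size or power for toxicity, so there is no toxicity figure to reproduce. Its only group sizes are for the primary outcome. The two-proportion formula with pooled variance (two-sided 5%, 80% power, no continuity correction) at 70% versus 50%, 55% and 60% returns 93, 163 and 356 per group, exactly as stated. I use 93 below only as a realistic group size.

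**Inputs, all assumed because the documents give none:**
- q: true rate of chemotherapy-related toxicity, the same in both groups (no real effect), from 30% to 90%.
- b: share of patients with a gradable symptom before the first dose, 30% of well-nourished and 60% of malnourished patients.
- m: fraction of those symptoms wrongly attributed to chemotherapy, the same in both groups.
- Baseline symptoms and true toxicity are independent.

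**Formula.** Observed rate = 1 − (1 − q)(1 − m·b). The false difference is therefore (1 − q)·m·(b in malnourished − b in well-nourished).

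**All baseline symptoms miscounted (m = 1):**

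| q | Well-nourished | Malnourished | False difference | Chance of p < 0.05, 93 per group |
|---|---|---|---|---|
| 30% | 1 − 0.7×0.7 = 51% | 1 − 0.7×0.4 = 72% | 21 points | 0.84 |
| 50% | 1 − 0.5×0.7 = 65% | 1 − 0.5×0.4 = 80% | 15 points | 0.63 |
| 70% | 1 − 0.3×0.7 = 79% | 1 − 0.3×0.4 = 88% | 9 points | 0.38 |
| 90% | 1 − 0.1×0.7 = 93% | 1 − 0.1×0.4 = 96% | 3 points | 0.14 |

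The last column is the normal-approximation power of a two-sided 5% comparison of the two observed rates.

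**Partial miscounting at q = 50%:**
- Half (m = 0.5): 1 − 0.5×0.85 = 57.5% versus 1 − 0.5×0.70 = 65%. The false difference is 7.5 points, flagged with probability 0.18.
- A quarter (m = 0.25): 0.5 × 0.25 × 0.30 = 3.75 points, flagged with probability 0.07.

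**Smaller baseline gap (20% versus 40%, m = 1):** (1 − q) × 0.20 gives 14, 10, 6 and 2 points at q = 30%, 50%, 70% and 90%.

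The bias shrinks in proportion to 1 − q. The commoner true toxicity is, the fewer patients are left to be misclassified.

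**The case against.** The case against is substantial, and much of it stands.

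- **The outcome is limited to chemotherapy-related events.** A reader might infer that the plan counts pre-existing symptoms as toxicity. It does not say so. Recording every adverse event in the CRF is not the same as defining the outcome. But the restriction works only if the assessor can tell old from new, and no graded baseline is named for that purpose.
- **Baseline data exist.** Weight loss, haemoglobin, albumin, fecal elastase, the anorexia/cachexia subscale and the QLQ-PAN26 are listed, and Visit 1 variables are checked again at Visit 2. This is real mitigation, and laboratory terms could be graded afterwards from stored values. A questionnaire score is not a toxicity grade, however. For fatigue and diarrhoea the article names no dedicated baseline item, and the Statistical Analysis section does not use the questionnaires to correct toxicity.
- **Visit 1 may cover adverse events.** Its wording can be read as including the treatment-related list. That list ties the toxicity scale to visit 2, so this reading adds no baseline grade.
- **A severity cut-off may sit in the full protocol.** Agreed. Its absence from an article is no finding, and making grade 3 or higher the only definition would be a preference.
- **A ceiling.** A reader might infer that nearly every patient will have some toxicity, so that the groups cannot differ. The article says intensified regimens can be harder to tolerate but gives no toxicity rate, so this is unsupported. It also pulls against the present point, since the false difference almost vanishes near a ceiling.
- **Exocrine insufficiency.** It does not define the cohort: it is not an eligibility criterion. It is a measured variable ("PEI will be defined by levels of fecal elastase-1 <200 mcg/g") and a candidate adjustment covariate.
- **Tolerance is measured elsewhere.** The primary outcome and the share of planned dose delivered do not depend on adverse-event grading, so it would be wrong to say that the study cannot address tolerance. They do not repair this outcome.

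**Conclusion.** The point holds as a risk of differential misattribution in one secondary outcome. The article fixes toxicity grading at Visit 2, names no pre-treatment grade, and compares the result between groups defined by a condition whose signs can resemble toxicity. Bias towards more apparent toxicity in malnourished patients cannot be excluded.

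Its size cannot be derived from the documents. With baseline symptoms assumed in 30% versus 60% of patients and all miscounted, the false difference runs from about 3 points (90% true toxicity) to 21 points (30%). It falls in proportion if only part are miscounted or the baseline gap is narrower. These figures show what could happen; they are not estimates for this cohort. Neither the primary outcome nor the 93, 163 and 356 per group is affected.

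**What to change.** Grade the same adverse-event terms at Visit 1, before the first dose, on the scale used at Visit 2, drawing on the history and blood tests already taken there. Count as toxicity only events that are new or worse than the Visit 1 grade. Report the results by grade, and show nutrition-type terms (anorexia, weight loss, low albumin, fatigue, diarrhoea) separately from the rest.

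The cost is one extra CRF page at an existing visit, a sentence in the outcome definition, and a somewhat lower reported toxicity rate. Two limits remain. Worsening caused by the tumour itself is not removed. A patient who starts at a high grade also has less room to worsen, which is a further reason to show the nutrition-type terms separately.

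For patients already enrolled without a baseline grade, laboratory terms can still be graded from Visit 1 values. Symptom terms should be reported with the caveat that pre-treatment severity was not graded.
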